#### Secondary outcomes

Improvement in neurological function at each appointment throughout the trial. Efficacy will be determined by a reduction of ≥ 50% or the total score of 0–1 in the 15-item National Institute of Health Stroke Scale (NIHSS) score (scores range from 0 to 42, whereby higher scores indicate a more severe neurological deficit) [27]The improvement in independence at each appointment as measured by a modified Rankin Scale (mRS) at each appointment throughout the trial (scores on this scale range from 0 to 6, with higher scores indicating greater disability) [28]The proportion of participants with a Barthel Index (BI) score of ≥ 90 at each appointment throughout the trial. The BI is used to evaluate the activities of daily living, ranging from 0 to 100, whereby higher scores indicate increased independence [29]The improvement of TCM syndrome at each appointment as measured by the reduction (reduction = (before treatment score − after treatment score)/before treatment score × 100%) in the following scale: clinical cure: reduction > 75%, markedly effective: reduction 51–75%, effective: reduction 25– 50%, invalid: reduction < 25% [30]

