### Sample size calculation

This is an exploratory clinical trial designed to provide scientific rationale and feasibility for clinical phase II pilot study and, therefore, is not fully powered. A sample size of 80 participants will be recruited, with 40 participants in each treatment group. Results from this study will be used to for sample size calculations in future studies.

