### Statistical analysis

All of the data from this study will be analyzed by biostatisticians using SPSS 20.0 (IBM Corp., Armonk, NY, USA). Outcomes are based on the intention-to-treat analysis.

Baseline characteristics will be summarized by means of simple descriptive statistics and be compared between two study groups to assess covariate balance. The two-sample Student’s *t* test will be used for continuous variables and the chi-square test or Wilcoxon test will be used for categorical variables.

The primary analysis will be a comparison of the efficacy on depression between the two groups after 8 weeks of treatment. Pearson’s chi-squared test will be used to analyze the effective cases and logistic regression will be used to adjust for chance imbalances in the main prognostic variables between groups, such as age and gender.

Secondary analyses will include the improved cases in neurological function (NIHSS score reduction of ≥ 50% or the total score of 0–1), independence (mRS 0, 1, and 2), daily living (BI scores ≥ 90), and TCM syndrome. Secondary outcome analyses will be carried out according to standard statistical principles for comparison of parametric or non-parametric distributions as appropriate. Logistical regression analysis will be used to adjust for chance imbalances in the main prognostic variables between groups, such as age, NIHSS scores, BI scores, and TCM syndrome scores.

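### The secondary mRS and Barthel endpoints are called improved cases but defined by the visit score alone, so unchanged and some worsened participants count as improved

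*Protocol article*

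**What the plan says.** All references are to the protocol article.

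- **Statistical analysis, label.** "Secondary analyses will include the improved cases in neurological function" opens a list that also covers independence, daily living and TCM syndrome.
- **Statistical analysis, rules.** NIHSS: "NIHSS score reduction of ≥ 50% or the total score of 0–1". mRS: "independence (mRS 0, 1, and 2), daily living". BI: "daily living (BI scores ≥ 90), and TCM syndrome". The mRS and BI rules contain only the score at the visit.
- **Secondary outcomes, mRS.** "The improvement in independence at each appointment as measured by a modified Rankin Scale (mRS"), with no cut-off and no rule for change.
- **Secondary outcomes, BI.** "The proportion of participants with a Barthel Index (BI) score of ≥ 90", which is a status and is not called improvement.
- **Secondary outcomes, NIHSS and TCM.** The NIHSS rule is the same as in the analysis section. TCM syndrome is a percentage reduction from the pre-treatment score.
- **Inclusion and Exclusion criteria.** Participants need a stroke with signs of neurological deficit. No minimum NIHSS or mRS and no maximum BI is set.
- **Adjustment.** Logistic regression for chance imbalance in prognostic variables, "such as age, NIHSS scores, BI scores, and TCM syndrome scores". Baseline mRS is not named.

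**The concern.** A participant counted as improved should be better than at entry. The mRS and BI rules cannot show this, because they never look at the entry score, and nothing in eligibility keeps out people who already meet the threshold. Such people are plausible: participants must be cooperative and free of aphasia and severe cognitive impairment, and recruitment includes community posters and Internet advertising.

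Two things are at stake. First, the trial may publish an improvement rate that is partly a description of who was enrolled. Daily living is part of the stated aim, and the Sample size calculation section says the results will feed the sizing of later studies, so an inflated rate would carry forward. Second, participants who start at target and stay there add equally to both arms and leave less room for a difference to appear.

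**Working it through.** The plan states no rate, power or effect size for these endpoints, so there is no figure to reproduce. The check has two parts.

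**1. Which score pairs count as improved?**

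Every baseline-to-visit pair was listed and the rule applied.

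| Scale and rule | Unchanged, counted | Worsened, counted | Better, not counted |
|---|---|---|---|
| mRS 0–2 (baseline 0–5) | 3: 0–0, 1–1, 2–2 | 3: 0→1, 0→2, 1→2 | 3: 5→4, 5→3, 4→3 |
| BI ≥ 90 (5-point steps) | 3: 90, 95, 100 | 3: 95→90, 100→95, 100→90 | 153 pairs ending below 90 |
| NIHSS ≥ 50% reduction or 0–1 (baseline ≥ 1) | 1: 1–1 | 0 | 420 pairs |

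If a baseline NIHSS of 0 were possible, 0–0 and 0→1 would count as well. The deficit criterion makes that unlikely. The same argument can be made against a baseline mRS of 0. Even so, mRS 1–1, 2–2 and 1→2 remain, and so do all six BI pairs. The counts show what the rules permit, not how often it will happen.

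**2. How much sensitivity is lost?**

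Inputs:
- 40 per arm, from the Sample size calculation section: "A sample size of 80 participants will be recruited, with 40 participants in each treatment group".
- Assumed, not in the document: a share *f* of each arm starts at target and stays there; among the rest, 20% (placebo) and 40% (JDTLG) reach target.

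Formulas:
- Observed rate = *f* + (1 − *f*) × rate among the rest.
- Difference = (1 − *f*) × (0.40 − 0.20).
- SE = √[(p₁(1 − p₁) + p₂(1 − p₂)) / 40].

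| *f* | Placebo | JDTLG | Difference | SE | Difference / SE |
|---|---|---|---|---|---|
| 0 | 20% | 40% | 20 points | 10.0 | 2.00 |
| 20% | 0.2 + 0.8 × 0.2 = 36% | 0.2 + 0.8 × 0.4 = 52% | 16 points | 11.0 | 1.46 |
| 40% | 0.4 + 0.6 × 0.2 = 52% | 0.4 + 0.6 × 0.4 = 64% | 12 points | 11.0 | 1.10 |
| 50% | 0.5 + 0.5 × 0.2 = 60% | 0.5 + 0.5 × 0.4 = 70% | 10 points | 10.6 | 0.94 |

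A larger assumed effect gives the same pattern. With 20% versus 50% among the rest and *f* = 0, 20%, 40% and 60%, the difference is 30, 24, 18 and 12 points. Power with 40 per arm (two-sided 5%) is about 82%, 58%, 38% and 23%.

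**The case against.** The case for leaving the plan alone has real substance.

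- **Status endpoints are legitimate.** The proportion at mRS 0–2 or BI ≥ 90 is a coherent outcome for a randomised comparison. Under the assumptions above with *f* = 40%, 12 points is the correct effect in all randomised participants; 20 points belongs to a different population, those below threshold at entry. This stands. The loss is of sensitivity, and there is no bias.
- **NIHSS.** A reader might infer that NIHSS is also a pure status rule and that worsened participants count there too. The documents do not support that. The rule has a branch for a reduction of at least 50%, and worsening counts only from a baseline of 0. What remains is the unchanged score of 1.
- **BI.** The Secondary outcomes section already words BI as a proportion. For BI the fault lies only in the analysis section's label.
- **Chance imbalance.** A reader might infer that baseline imbalance passes unchecked into the result and is as large as the diluted effect. Adjustment for NIHSS and BI is already planned, and the covariate list gives examples, so mRS is not excluded. The SE of the chance difference in baseline share, √[2*f*(1 − *f*)/40], is 8.9, 11.0 and 11.2 points at *f* = 20%, 40% and 50%, against differences of 16, 12 and 10, so the comparison fails at 20%. Nor is this an extra error: it is already part of the sampling variance of the final comparison.
- **Restricting to those below threshold.** At *f* = 40% this leaves 24 per arm and an SE of √[(0.16 + 0.24)/24] = 12.9 points, a ratio of 1.55 against 1.10. Sensitivity improves, but prevention of deterioration in the others is no longer seen. That is a trade-off, and the plan is not wrong for declining it.

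None of this answers the label. Adjustment does not change who is counted as improved, and the two sections describe the mRS and BI outcomes differently.

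**Conclusion.** The point holds for mRS and BI, and narrowly for NIHSS. Followed as written, the analysis reports unchanged participants, and some who worsened on mRS or BI, as improved, and it conflicts with the outcome definitions in the same article. This rests on the text alone and needs no assumption.

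The loss of sensitivity does rest on assumptions, because the baseline distribution is not given. At assumed rates of 20% versus 40%, a 20-point difference becomes 16, 12 or 10 points if 20%, 40% or 50% start at target. If few start there, the loss is small.

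The documents do not support a claim of bias or of an advantage to either arm. The HAMD-17 primary outcome is outside this point, and TCM syndrome is change-based. For secondary outcomes of an exploratory pilot this is a moderate matter, worth correcting because it costs so little.

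**What to change.** 1. In the Statistical analysis section, stop calling mRS 0–2 and BI ≥ 90 improved cases. Report them as the proportion independent, and the proportion with BI ≥ 90, at each visit. Word the Secondary outcomes section to match.
2. Adjust each endpoint for its own baseline value, and add baseline mRS to the named covariates.
3. If improvement in independence is to be claimed, base it on an ordinal mRS analysis (proportional odds) adjusted for baseline mRS.
4. For NIHSS, state that a participant with a baseline score of 0–1 cannot count as improved without a reduction.

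Cost: a few sentences of wording, slightly more analysis and a less simple presentation. No new data are needed, since the Study visits and procedures section has secondary outcomes collected from baseline.

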### Study visits and procedures

The visit schedule for all evaluations (baseline, primary outcomes, secondary outcomes, exploring outcomes and safety indicators) is shown in Table 1. Participants will be assessed by the same investigator at each assessment. Baseline measurements, demographic characteristics, and medical history will be collected at the first visit only. All concomitant medications will be recorded during the treatment period (i.e., baseline to 8 weeks), including the name, dosage, and course of these medications. Primary and secondary outcomes and safety indicators will be collected every 4 weeks from baseline until week 16.

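### The model for mRS 0–2 is not sure to contain baseline mRS: the illustrative covariate list leaves it unnamed and adjustment is tied to chance imbalance

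*Protocol article*

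**What the plan says.** The Secondary outcomes section has four scales: NIHSS, mRS, BI and TCM syndrome. The mRS outcome there is "The improvement in independence at each appointment as measured by a modified Rankin Scale (mRS) at each appointment throughout the trial". The Statistical analysis section counts improved cases on each scale and turns the mRS outcome into a status; its list ends with "independence (mRS 0, 1, and 2), daily living (BI scores ≥ 90), and TCM syndrome".

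The basic comparison is described in general terms: "Secondary outcome analyses will be carried out according to standard statistical principles for comparison of parametric or non-parametric distributions as appropriate". Logistic regression is then added to "adjust for chance imbalances in the main prognostic variables between groups, such as age, NIHSS scores, BI scores, and TCM syndrome scores". The matching sentence for the primary outcome refers to "main prognostic variables between groups, such as age and gender".

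On data collection, the Study visits and procedures section says: "Primary and secondary outcomes and safety indicators will be collected every 4 weeks from baseline until week 16". Table 1 cannot be read in the copy at hand, so the availability of baseline mRS rests on that sentence. Neither the inclusion nor the exclusion criteria set a limit on mRS.

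On size: "A sample size of 80 participants will be recruited, with 40 participants in each treatment group". The same section says that the trial "is not fully powered".

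**The concern.** Two features of the adjustment sentence combine badly for the mRS endpoint. It gives examples that cover three of the four secondary scales and passes over the fourth. It also makes chance imbalance the reason to adjust, although a strongly prognostic baseline helps the comparison whether or not the arms happen to differ on it.

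Where a participant starts on the 0–6 scale can be expected to bear strongly on whether that participant is at 0–2 eight weeks later. Without baseline mRS, NIHSS and BI can stand in for it only in part. At stake are some power for the independence comparison and a clean reading of the result as improvement. The Sample size calculation section says the results will feed the planning of later studies, so the estimate will be reused.

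**Working it through.** **Step 1. Set the four endpoints side by side** (Secondary outcomes and Statistical analysis sections).

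| Endpoint as analysed | Baseline value in the definition? | Own scale among the named covariates? |
|---|---|---|
| NIHSS: fall of at least 50%, or total 0–1 | In part | Yes |
| mRS 0–2 | No | No |
| BI of at least 90 | No | Yes |
| TCM syndrome: graded by percentage reduction | Yes | Yes |

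Only mRS has a no in both columns.

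**Step 2. How large a chance imbalance could be.** Assume that half of the participants start at mRS 0–2 (the document gives no figure). The standard error of the between-arm difference in that share is sqrt(2 × 0.5 × 0.5 / 40) = sqrt(0.0125) = 0.112. The 95% range is ±1.96 × 0.112 = ±0.22, or about 22 percentage points either way.

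**Step 3. Cost in power of leaving baseline mRS out.** The document gives no alpha, effect size, event rate or power, so there is no stated figure to reproduce and every input below except the sample size is an assumption.

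- 80 participants, 1:1; two-sided 5% test; 2,000 simulated trials per scenario.
- 50% at mRS 0–2 on placebo; latent treatment shift 0.6 SD, so about Φ(0.6) = 73% on active treatment.
- Latent baseline mRS correlates 0.5 or 0.7 with week-8 mRS, and 0.5, 0.7 or 0.8 with each of NIHSS and BI. Baseline mRS enters the model as an ordinal score.
- Age was generated as unrelated to outcome, and the TCM score was not simulated.

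| Baseline to week-8 mRS | mRS with NIHSS and BI | Unadjusted | Age + NIHSS + BI | Same + baseline mRS | Gain (points) |
|---|---|---|---|---|---|
| 0.5 | 0.5 | 58.7% | 59.9% | 63.3% | 3.4 |
| 0.5 | 0.7 | 53.7% | 56.7% | 58.8% | 2.1 |
| 0.5 | 0.8 | 56.8% | 60.0% | 61.0% | 1.0 |
| 0.7 | 0.5 | 54.2% | 58.4% | 67.6% | 9.2 |
| 0.7 | 0.7 | 54.9% | 62.1% | 67.9% | 5.8 |
| 0.7 | 0.8 | 55.7% | 65.2% | 66.9% | 1.7 |

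With no treatment effect, the models adjusted for age, NIHSS and BI, with or without baseline mRS, rejected in 4.6% to 5.6% of trials. Each power figure has a Monte Carlo standard error of about sqrt(0.6 × 0.4 / 2000) = 1.1 points. The gains should be compared within a row, and the smallest ones not read finely.

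A model with treatment and baseline mRS alone did as well as the full one (58.9% to 67.7% across the six rows). That is partly by construction, since NIHSS and BI carried no information here beyond baseline mRS.

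**Step 4. Why the loss is power and not standard error.** In the row with correlations 0.7 and 0.5, adding baseline mRS raised the median standard error of the log odds ratio from 0.541 to 0.651, while the median log odds ratio rose from 1.160 to 1.523. The ratio of the two went from 1.160 / 0.541 = 2.14 to 1.523 / 0.651 = 2.34. In the row with 0.5 and 0.8, the standard error went from 0.544 to 0.564 and the ratio from 1.187 / 0.544 = 2.18 to 1.250 / 0.564 = 2.22. Without the covariate, the odds ratio sits closer to 1.

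**The case against.** The strongest reply is that the article does not omit anything. Its covariates are examples, given once for all secondary endpoints together, and a closed list for each endpoint normally belongs in an analysis plan that is not shown. This stands against a reading that a reader might infer: that independence will be analysed without its own baseline. The text does not say so.

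A second reply is that the sentence already covers real imbalance. If baseline mRS is prognostic and the arms differ on it, the stated principle would bring it in. That also stands. It does not answer the case where the arms look balanced: there the principle gives no reason to adjust, and the power is given up. This weakness affects every adjusted model in the section. It bears most on mRS 0–2, which has no other protection. For the primary outcome, baseline HAMD-17 is likewise unnamed. That is a separate and weightier matter.

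Third, the size rests on assumptions. The TCM score is a named covariate and its diagnostic signs include hemiplegia, so it may carry some disability information and shrink the gain. A variant with a 0.65 SD shift and a baseline-to-week-8 correlation of up to 0.8 gave gains of up to 14 points, but type I error had risen to about 7% there, so the top of that range is not relied on.

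Finally, this is one of four secondary outcomes in a trial that makes no claim to full power. That limits the weight of the point, not its correctness.

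**Conclusion.** The point holds in a limited form. The plan does not secure baseline mRS in the model for mRS 0–2, the one secondary endpoint whose baseline appears neither in its analysed definition nor among the named covariates. The expected cost of leaving it out is about 1 to 9 points of power at 40 per arm, and 1 to 2 points if NIHSS and BI correlate 0.8 with mRS. All correlations, rates and effects behind this range are assumed.

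Two stronger inferences are not supported. The documents do not show that baseline mRS will be excluded. Nor would leaving it out make the randomised comparison invalid: participants who start and stay at 0–2 count as improved in both arms alike, and simulated type I error stayed near 5% without baseline mRS. What suffers is power, and the reading of a status as improvement. This is a minor point.

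**What to change.** In the Statistical analysis section, state that the logistic model for mRS 0–2 always contains treatment, age and baseline mRS as an ordinal score, whether or not the arms look imbalanced. Add that each secondary model always contains the baseline value of its own scale. Odds ratios from models with different covariates are not interchangeable, so fixing the set in advance also makes the estimate easier to reuse in planning.

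The cost is a sentence or two. No new data are needed if baseline mRS is collected as the Study visits and procedures section says; the visit schedule should be checked to confirm it. The small downside is one more covariate in a model of 80 participants.

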## Discussion

Depression is common after stroke and is related to with poor functional outcome and high mortality [33]. The association between depression and stroke has been established whereby stroke has been shown to increase the risk of PSD, and conversely, depression has been shown to be an independent risk factor for stroke [34]. The most commonly used antidepressants are SSRI and SNRIs, although they are not without side effects including increasing risk of hemorrhagic complications. As antidepressant medications have the potential to cause a series of adverse effects and are associated with poor patient compliance, it is important to explore other effective treatments that may have fewer side effects in the management of PSD. Chinese herbal medicine has the potential to offer an effective and safe treatment for PSD.

In this trial, we will investigate whether the JDTLG plus conventional treatment can reduce depression and improve daily living ability among participants who have recently suffered a stroke. We have previously shown that JDTLG effectively treats PSD in a rat model. This study will be conducted as a randomized, double-blind, placebo-controlled pilot crossover trial to provide evidence for the clinical efficacy of JDTLG.

The purpose of this prospective trial is to prove the therapeutic efficacy and safety of JDTLG. The outcome of the trial will provide evidence-based data regarding whether JDTLG is beneficial for PSD participants with qi deficiency and blood stasis syndrome. More importantly, the success of this study will support a large-scale clinical study to further consolidate the evidence for the use of JDTLG in PSD patients with qi deficiency and blood stasis syndrome.

This study has several limitations that require consideration. Firstly, as the study is being undertaken in one center; therefore, it may not necessarily be possible to extrapolate these results to other regions or ethnic groups. Secondly, the sample size is small and the treatment period short. However, this data will inform a subsequent multi-centered study compromising a sufficient sample size over a longer treatment period.

In conclusion, this prospective study will demonstrate that the JDTLG with conventional treatment is able to effectively and safely treat PSD with qi deficiency and blood stasis syndrome, thereby providing a new direction for treating PSD with minimal side effects.

### Trial status

The trial was initiated in April 2017 and is currently recruiting participants.

## Abbreviations

AEs: Adverse events
BI: Barthel Index
CDMS: Clinical data management system
CRF: Case report form
CT: Computed tomography
ECG: Electrocardiogram
HAMD-17: 17-item Hamilton Depression Scale
IL: Interleukin
MRI: Magnetic resonance imaging
NIHSS: National Institute of Health Stroke Scale
PSD: Post-stroke depression
SNRI: Serotonin and norepinephrine reuptake inhibitors
SSRI: Selective serotonin reuptake inhibitors
TCM: Traditional Chinese medicine
